### Study Setting

This trial is being conducted in Kampala, which is the capital of Uganda. Uganda’s progressive refugee policies provide refugees and displaced persons in refugee settlements a plot of land. Yet, with the 2006 Uganda Refugee Law, refugees forgo rights to humanitarian assistance if they leave these refugee settlements [16,17]. The convergence of this law with refugee urbanization contributes to extreme poverty among Kampala’s urban refugees, creating slum environments [16,36,37]. Among Ugandan youth aged 15 to 19 years, the HIV prevalence is estimated at 4% [38]. However, among vulnerable youth living in Kampala’s informal settlements, this is estimated at 37.2% [39]. The five informal settlements selected for this study are grouped into three sites based on their proximity to one another (Kabalagala/Kansanga, Katwe/Nsambya, and Rubaga) and have been purposively chosen because these communities host many displaced/refugee persons in Kampala [16,18,36,37]. We focused on these refugee communities, largely from the Democratic Republic of Congo, Rwanda, and Burundi [13], where refugees continue to arrive, owing to similarities in socioeconomic status and living conditions, health care access, and shared languages (French and Swahili).

### Study Population and Eligibility Criteria

A minimum of 432 youth (144 per cluster) between the ages of 16 and 24 years will be enrolled into this study and followed for 12 months. Individuals are eligible for inclusion if they meet the following criteria: (1) currently live in one of the following five informal settlements in Kampala: Kabalagala, Kansanga, Katwe, Nsambya, and Rubaga; (2) identify as a refugee/displaced person or have refugee/displaced parents; (3) are aged 16 to 24 years; (4) speak English, Swahili, Luganda, French, Kinyarwanda, or Kirundi; and (5) own a mobile phone. A brief eligibility screening (via phone, in person, or via WhatsApp) with interested participants will be conducted, asking self-reported HIV serostatus. Only participants reporting an HIV-negative status (baseline serostatus) will be eligible to participate.

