## Introduction

HIV is the leading cause of death among young people globally and the main cause of death among adolescents and young people in sub-Saharan Africa [1]. In sub-Saharan Africa, half of newly infected adolescents and young people are girls [2,3]. Uganda’s 2018 HIV prevalence among adolescent girls was over double that of adolescent boys, with 14,000 young women aged 15 to 24 reporting new HIV infections compared with 5000 young men [4]. Only 53.6% of adolescent girls in Uganda know their HIV status, and this is far below the Joint United Nations Program on HIV/AIDS (UNAIDS) goal of 90% of persons living with HIV knowing their status by 2020 to achieve an AIDS-free generation [5,6]. HIV testing is a critical entry point for access to HIV prevention and control solutions, specifically access to antiretroviral therapy, which is vital for preventing onward HIV transmission [7,8].

There are more than 79.5 million forcibly displaced persons worldwide [9], and refugee and displaced persons are largely underserved by current HIV prevention strategies [10]. HIV vulnerabilities among displaced/refugee adolescents are shaped by a complex interplay of factors, including poverty, violence, host community HIV prevalence, urbanization, HIV testing and care access, and living conditions [10-12]. Uganda hosts more than 1.4 million refugees [13], with 62% aged below 18 years [14]. Kampala, Uganda’s capital city, hosts over 83,000 refugees [13], and 27% are aged 15 to 24 years [15]. It is important to explore HIV testing needs among urban refugees. There is a global trend of refugee urbanization, with refugees increasingly moving from refugee settlements to urban areas for employment and education opportunities [16-19]. Urban refugees and displaced adolescents and young people are at the nexus of HIV disparities among adolescents, displaced persons, and slum dwellers, and yet, there are knowledge gaps in the optimal HIV prevention for these groups [20,21].

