## Methods

### Study Aim and Objectives

This study aims to evaluate the feasibility and clinical effectiveness of two HIV self-testing delivery approaches (HIV self-testing intervention alone and HIV self-testing combined with a two-way supportive SMS mHealth intervention) in comparison with the standard of care in terms of HIV testing uptake among refugee and displaced youth aged 16 to 24 years in Kampala, Uganda. The specific objectives of this study are to determine the effectiveness of the interventions on the following criteria: (1) increased frequency of HIV testing; (2) increased knowledge of HIV status; (3) increased linkage to confirmatory testing (for those with an HIV positive self-test); and (4) increased linkage to HIV care (for persons testing positive for HIV in HIV self-testing and confirmatory testing). Secondary outcomes include (1) depression, (2) condom use self-efficacy, (3) consistent condom use, (4) sexual relationship power, (5) HIV stigma, and (6) adolescent sexual and reproductive health (SRH) stigma.

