### Patient and Public Involvement in Research

Study collaborators at Young African Refugees for Integral Development (YARID) have been involved in the research from the initial stage of developing the research question and focus. We conducted a preliminary exploration of the needs and priorities of refugees and youth with YARID prior to developing this study, and those findings indicated a low prevalence of lifetime HIV testing, which reinforced the importance of this study. Peer navigators, who themselves are urban refugee youth living in Kampala’s informal settlements, provided feedback for the study design and outcomes; conducted recruitment and active engagement with study participants for retention; supported study implementation by facilitating linkages between participants and data collectors; pilot tested the survey to assess the time required to participate in the research; and will engage in multiple dissemination strategies for community members (eg, providing input for infographic design and sharing community reports with community stakeholders including the Ministry of Health).

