### Outcomes

#### Primary Outcomes

The primary outcomes measured in this trial are as follows:

Changes in HIV testing frequency: This is measured as participants’ self-reported last HIV test. To capture changes, this measure is assessed at all three study time points (baseline [Time 1], 8 months [Time 2], and 12 months [Time 3]).Changes in knowledge of HIV status: To address social desirability bias challenges regarding self-reported HIV serostatus, multiple steps are employed. First, at each timepoint (Time 1, Time 2, and Time 3), participants are asked their current HIV status. At Time 3, participants are offered a completely voluntary rapid HIV test. Knowledge of HIV status will be assessed as correct for persons who agree to take the rapid test and correctly report their HIV status (prior to receiving the result).Changes in linkage to confirmatory HIV testing: Participants in trial arms 1 and 2 (HIV self-testing and mHealth HIV self-testing intervention) are asked at Time 2 and Time 3 if they used their HIV self-testing kit. For those who respond affirmatively, they will be asked the result, and those who report a positive result will be asked if and where they received confirmatory testing.Changes in linkage to HIV care: Participants who seroconvert during the study are asked the frequency of accessing HIV care service since diagnosis. This will be assessed at Time 2 and Time 3.HIV self-testing kit use: To understand the frequency of HIV self-testing kit use and to reduce social desirability bias regarding HIV self-testing kit use, participants in trial arms 1 and 2 will be followed up 1 month after Time 3 to request for purchasing unused kits back. Participants will not be informed of this as an option prior to this time.

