### Sample Size and Power Analysis

Cluster sizes of 130 per group (n=390) are required to have 80% power (*P*<.05) to detect a 25% difference (39% [5] vs 64% tested) in HIV testing between any two groups from three pairwise comparisons (control vs arm 1, control vs arm 2, and arm 1 vs arm 2) for an odds ratio of 1.66. We assume an intraclass correlation coefficient of 0.013 based on HIV research on condom use in sub-Saharan Africa [50]. With 10% attrition, 432 participants (144 per cluster) are required. Computations were performed using RStudio version 3.3.0 (RStudio Team), based on formulae for multiple comparisons of proportions, and adjusted for design effect [51].

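### Entry requires a reported HIV-negative status, so status knowledge cannot be analysed as a change from Time 1, and it is unclear whether unknown-status youth could enrol

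*Protocol article*

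**What the plan says.** The protocol article, Study Population and Eligibility Criteria, describes a brief screening contact "asking self-reported HIV serostatus", and then sets the rule: "Only participants reporting an HIV-negative status (baseline serostatus) will be eligible to participate". No test and no proof of a past test is described at this step, and no category is given for people who do not know their status.

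The trial is motivated by gaps in testing and in status knowledge. The Introduction says "Only 53.6% of adolescent girls in Uganda know their HIV status". Under Patient and Public Involvement in Research, the article reports preliminary work with the community partner and adds that "those findings indicated a low prevalence of lifetime HIV testing, which reinforced the importance of this study".

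Status knowledge is also an objective and a primary outcome. Study Aim and Objectives lists "2) increased knowledge of HIV status". The Primary Outcomes section labels the outcome as a change and says that "at each timepoint (Time 1, Time 2, and Time 3), participants are asked their current HIV status". The same section offers a voluntary rapid test at Time 3 only. It scores knowledge as correct when a participant takes that test and had reported the matching status before seeing the result.

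**The concern.** A person who has never tested, or does not know the result, cannot truthfully report being negative. Taken literally, the rule admits only those who say they already have a negative status, while the article presents missing status knowledge as a main reason for the trial.

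Two things are at stake. The first is the status-knowledge outcome: if everyone must give the same answer to get in, there is no starting variation and no room for improvement. The second is the population to which the results apply. Readers cannot tell whether unknown-status youth were turned away, or were admitted and recorded as negative.

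**Working it through.** The plan gives no figure on this point to reproduce. The check sets the entry rule beside the outcome definition.

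**Inputs**
- Entry rule: must report negative (Study Population and Eligibility Criteria).
- Basis of the report: unverified self-report (same section).
- Reported status: asked at Times 1, 2 and 3 (Primary Outcomes).
- Verified status: rapid test at Time 3 only (Primary Outcomes).

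**Step 1: reported knowledge.** Let R be the percentage reporting a known status. The eligibility section treats the screening answer as baseline serostatus, so R at Time 1 is 100% by construction. Later R can be at most 100%. Hence R(Time 3) − R(Time 1) = R(Time 3) − 100 ≤ 0. The objective is an increase, and this measure can only stay level or fall. A participant who answered the Time 1 survey differently from the screening question would be an exception, but would then not have met the entry rule as written.

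**Step 2: verified knowledge.** Let V be the percentage whose report is confirmed as correct. V(Time 3) can be observed in those who accept the test. No test is described at Time 1, so V(Time 1) is unmeasured and V(Time 3) − V(Time 1) cannot be computed. The true V(Time 1) may be below 100%, because some who report negative may have an undiagnosed infection, but nothing collected shows this.

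**Step 3: mixing the two.** Using the Time 1 report as the baseline for the Time 3 verified measure gives V(Time 3) − 100, which changes the definition between visits. Between arms A and C the constant cancels: [V_A(Time 3) − 100] − [V_C(Time 3) − 100] = V_A(Time 3) − V_C(Time 3). What can be estimated is the between-arm difference at Time 3. The Time 1 answer adds nothing to it.

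**Step 4: who can enter.**
- Knows they are negative and says so: enters.
- Truthfully answers unknown or never tested: no route in the text.
- Never tested, believes they are negative and says so: enters, recorded as negative.

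The documents do not give the size of the second or third group.

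**The case against.** Five points can be made for the plan.

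1. The aim and the strengths name refugee and displaced youth, not untested youth. The first objective, more frequent testing, fits people who have tested before. This stands: it is an inference from the background and the public-involvement section that untested youth are the group the trial is for.
2. Screening is unverified, so never-tested youth who believe they are negative can enter. The intent may have been only to screen out known positives. This also stands, and it means that the rule does not shut out all never-tested youth. The text still provides nothing for someone who says they do not know.
3. A condensed article may leave the coding of don't-know answers to the full protocol. This is fair for the form itself. But the article states an entry rule and a primary outcome that do not fit together, and that conflict does not depend on omitted detail.
4. Knowledge is already scored at Time 3 and the Data Analysis Plan specifies between-group comparisons, so the planned analysis may be close to what is needed. This largely stands. The change label and the increase objective remain unsupported.
5. The rule applies to every arm, so it does not in itself bias the testing comparison. This stands in full.

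A reader might also infer that about half of the intended population was excluded or miscoded, from 100 − 53.6 = 46.4% or, using the sample-size rates ("39% [5] vs 64% tested"), from 100 − 39 = 61%. The documents do not support this. The 53.6% concerns adolescent girls nationally. The 39% has no stated recall window, and someone tested some years ago could count as untested there and still report a negative status. Neither figure measures the share excluded.

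**Conclusion.** The concern holds in a limited form. As written, the entry rule fixes reported status at entry, and correctness is measured only at Time 3. The primary outcome on status knowledge therefore cannot be computed as a change from Time 1. This follows from the text, on the assumption that the rule was applied as stated.

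The rule also leaves open whether unknown-status youth were turned away or entered as negative, which bears on the population the conclusions can describe. The size of this effect cannot be given, because the documents contain no figure for the share excluded or miscoded.

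It would go too far to say that the trial excluded all untested youth, or that the arm comparison on testing is biased by this rule. Unverified self-report contradicts the first, and the common application of the rule across arms contradicts the second.

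**What to change.** 1. Define the status-knowledge outcome as a between-arm comparison at Time 3 and drop the change-from-Time-1 label. This is a wording change close to the existing scoring rule.
2. State how people who answered unknown or never tested were handled at screening, and reconcile the eligibility section with it. If they were enrolled, reword the criterion to *not self-reporting HIV-positive*. If they were not, limit the conclusions to youth who already report an HIV-negative status.
3. Adjust the testing outcome for baseline testing history, using the last-HIV-test item already asked at Time 1. Use a never-tested category only if that answer was recorded and varies; if it does not vary, the category has no use.

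The cost is wording and one covariate. Recruitment of 452 participants is complete and none of this needs re-enrolment. The Results section placed the final wave in February to March 2021, so at publication these points could still be settled before the final analysis. The downside is a narrower stated population if unknown-status youth were excluded.

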### Participant Recruitment and Retention

The project team includes a refugee youth-focused community-based nongovernment organization that implements economic empowerment programs for refugee youth and holds expertise on youth engagement. The team also involves academics and practitioners from the Ministry of Health and HIV clinics. Additionally, this project engages peer navigators who identify as refugees or displaced persons (aged 18-24 years) to help with participant recruitment and to provide feedback on the study design and survey. Twelve peer navigators (six young women and six young men) recruited for this study have been identified by community-based collaborators, have experience working in the various study communities as health or peer educators, and are deeply respected and connected in their communities.

Participants will be recruited within each settlement using purposive methods, including word-of-mouth and venue-based sampling at refugee agencies and community events. Peer navigators will conduct peer-driven recruitment at each site, sharing youth-designed flyers for potential participants to contact (via email and mobile number) peer navigators to join the study. Community collaborators and peer navigators will facilitate participant retention. Specifically, peer navigators will use multiple study reminder strategies (eg, social media and texts) to maintain engagement. We will utilize existing outreach and services by local refugee agencies and community partners.

### Patient and Public Involvement in Research

Study collaborators at Young African Refugees for Integral Development (YARID) have been involved in the research from the initial stage of developing the research question and focus. We conducted a preliminary exploration of the needs and priorities of refugees and youth with YARID prior to developing this study, and those findings indicated a low prevalence of lifetime HIV testing, which reinforced the importance of this study. Peer navigators, who themselves are urban refugee youth living in Kampala’s informal settlements, provided feedback for the study design and outcomes; conducted recruitment and active engagement with study participants for retention; supported study implementation by facilitating linkages between participants and data collectors; pilot tested the survey to assess the time required to participate in the research; and will engage in multiple dissemination strategies for community members (eg, providing input for infographic design and sharing community reports with community stakeholders including the Ministry of Health).

### Intervention Description

The study has been designed as a three-arm cRCT consisting of two treatment arms and one control arm. Clusters will be randomized to one of the following three arms: (1) HIV self-testing, (2) HIV self-testing plus mHealth strategies (supportive text messages), and (3) standard of care (clinic-based HIV testing). The trial arms and interventions are described below and summarized in Figure 1.

**Figure 1 figure1:**
[figure not shown]
Study design for Tushirikiane, a cluster randomized trial of a mobile health (mHealth) HIV self-testing strategy among urban refugee and displaced youth in Kampala, Uganda. SRH: sexual and reproductive health.

#### Treatment Arm 1: HIV Self-Testing Intervention

Participants in this arm will be enrolled into the HIV self-testing intervention group and will receive HIV self-testing kits so they can perform HIV testing. At baseline enrollment, the peer navigator will provide an HIV self-testing kit (OraQuick Rapid HIV-1/2 Antibody Test, OraSure Technologies), which includes an oral swab test stick and tube solutions, a written detailed step-by-step description of how to correctly use the HIV self-testing kit, pictorial and written guides for the HIV self-testing kit, condoms and lubricant, information booklets on HIV and testing, and referral cards with the addresses and phone numbers of local clinics for confirmatory testing. The cards will also have the peer navigator’s phone number to allow participants to contact the peer navigator if they need additional information on how to use the kit or need support to go for confirmatory tests at local clinics. Instructions for the kit are in French, Luganda, Swahili, Kirundi, Kinyarwanda, and English and have been pilot tested for clarity and comprehensiveness with peer navigators. A 24-hour contact number will be provided to participants to text if/when they have questions. At follow-up visits, peer navigators will check in with participants about the HIV self-testing kit, distribute another HIV self-testing kit and condoms/lubricant, and screen for adverse events (eg, negative HIV self-testing–related experiences).

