#### Treatment Arm 2: HIV Self-Testing Plus mHealth

Participants in this arm will be enrolled into the HIV self-testing group (as above) and on a web-based SMS platform hosted by WelTel [40,41]. WelTel is a nonprofit agency developing the mHealth intervention, in which participants receive weekly supportive bidirectional text messages asking how they are doing [42]. Participants are requested to reply “fine” or “not fine,” and those responding “not fine” will be contacted with support by a peer navigator. Participants in this arm will discuss the weekly WelTel messages with peer navigators and respond to the “not fine” messages within 2 days. If they do not reply to the initial SMS message within the specified timeframe, a peer navigator will follow up with them during that week. The WelTel system will manage the SMS intervention on a structured mobile phone platform (all SMS interactions are logged). WelTel’s two-way texting mHealth intervention may prompt participants to engage in HIV self-testing and/or to engage peer navigator support in decision making regarding HIV self-testing practices.

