#### Arm 3: Standard of Care

Participants in this arm will be enrolled into a standard of care group. Participants will receive information about HIV testing, care, and support services at local clinics. They will be provided a pamphlet of information about HIV and HIV prevention strategies (written in French, English, Luganda, Kirundi, Kinyarwanda, and Swahili).

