### Ethics

The study population includes young adults (aged 16 years or above) capable of providing informed consent; Uganda’s HIV and AIDS Prevention and Control Act permits youth aged 12 years or above to independently access HIV testing and counselling without parental permission. All participants will receive information about the study before being enrolled to ensure understanding of rights for refusal/withdrawal, study processes, and expectations, and to provide written informed consent. At any time during the study data collection period, participants can withdraw from the study before completing the interview with no adverse consequences on the care or services they receive. All data will be stored on password-protected computers. To maintain confidentiality, all participants will be given a unique case ID, and no personal identifying information will be stored with the study data.

The risks associated with the Tushirikiane trial are reasonable. Physical risks exist for participants who conduct HIV testing (standard of care) and/or confirmatory testing (HIV self-testing and HIV self-testing plus mHealth). However, in all cases, HIV testing and confirmatory testing are optional. Further, the results will only be linked to participant ID. Second, an HIV diagnosis may cause stress, anxiety, and fear of stigmatization among participants. Such risks will be mitigated by the clinics conducting testing, which offer confidential pretest and posttest counselling, as well as HIV treatment. All participants will also be provided with a list of community resources regardless of HIV testing outcomes.

Any adverse event will be reported by the peer navigator to the research assistant, who will fill out an adverse event reporting form (Adverse Event Reporting Form) and adverse event narrative form if appropriate (Adverse Event Narrative Form). Adverse events can also be directly reported by study participants via a Tushirikiane hotline, which will be shared with the study participants at enrollment (Template HIV Counselor Hotline Card), can be called toll free, and will be monitored by trained HIV counselors throughout the duration of the study. Any adverse event requiring a narrative form will be reported to the principal investigators within 24 hours.

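### Active adverse-event screening is stated only for the two self-testing arms, so adverse-event counts by arm would be open to unequal ascertainment

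*Protocol article*

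**What the plan says.** The protocol article deals with adverse events in two places: the arm descriptions and the Ethics section.

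- **Arm 1 (Treatment Arm 1: HIV Self-Testing Intervention).** At follow-up visits the peer navigator checks in about the kit and is to "distribute another HIV self-testing kit and condoms/lubricant, and screen for adverse events (eg, negative HIV self-testing–related experiences"). The screen is written as part of the kit visit.
- **Arm 2 (Treatment Arm 2: HIV Self-Testing Plus mHealth).** The cross-reference to arm 1 is made at the start of the section: "Participants in this arm will be enrolled into the HIV self-testing group (as above) and on a web-based SMS platform hosted by WelTel". The arm 1 procedures carry over. In addition, "participants receive weekly supportive bidirectional text messages asking how they are doing", and "those responding “not fine” will be contacted with support by a peer navigator". Those who do not reply are also followed up by a navigator.
- **Arm 3 (Arm 3: Standard of Care).** "Participants will receive information about HIV testing, care, and support services at local clinics", together with a pamphlet. No adverse-event screen is mentioned.
- **Ethics, reporting routes.** "Any adverse event will be reported by the peer navigator to the research assistant, who will fill out an adverse event reporting form". Then: "Adverse events can also be directly reported by study participants via a Tushirikiane hotline". Neither route is limited to an arm.
- **Ethics, harms foreseen.** Physical risk is named for testing in standard of care and for confirmatory testing in the self-testing arms. The section adds that "an HIV diagnosis may cause stress, anxiety, and fear of stigmatization among participants".

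Adverse events are not among the primary or secondary outcomes, and the Data Analysis Plan names no comparison of them between arms.

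**The concern.** How often a harm is recorded depends on how often it happens and on how hard the study looks for it. Here the stated effort to look is tied to the arm: a scheduled screen in arm 1, the same screen plus frequent contact in arm 2, and no stated screen in arm 3. For harms that can occur in every arm, such as distress after a positive result, a higher count in arms 1 and 2 could come from the asking alone. Similar counts would not show similar safety.

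A statistical analysis plan cannot repair this, because a harm that was never asked about cannot be recovered in analysis. What is at stake is the reading of any table of adverse events by arm. The trial sets self-testing against clinic-based testing, and readers of such a table will tend to compare its columns whether or not a test is planned.

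**Working it through.** The protocol gives no adverse-event rate and no detection rate, so there is no planned figure to reproduce. The check sets the stated procedures side by side and then shows how detection carries through to counts.

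**Step 1: stated routes by arm**

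| Route | Arm 1 | Arm 2 | Arm 3 |
|---|---|---|---|
| Active screen at follow-up visits | stated | stated, by cross-reference | not stated |
| Weekly two-way text with navigator response | no | stated | no |
| Navigator reports any adverse event to the research assistant | not limited by arm | not limited by arm | not limited by arm |
| Participant hotline | not limited by arm | not limited by arm | not limited by arm |
| Survey at 8 and 12 months | yes; adverse-event items not stated | same | same |

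The last three rows are common to all arms; the first two are not. The weekly text is an intervention component and is not described as an adverse-event screen. It does, however, give a navigator regular occasions to hear of a problem. The navigator route in the third row passes on what a navigator has learned. The text gives the navigator no task of asking about harms in arm 3.

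**Step 2: which harms are exposed to the difference**

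The one example given for the screen, bad experiences with self-testing, concerns kits that the study does not give to arm 3. For that category the asymmetry follows from the intervention. It is marked as an example, though, and not as the limit of the screen. The physical and psychological harms in the Ethics section apply to standard of care as well, and these are the ones sought unequally.

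**Step 3: effect on counts (illustration; all rates assumed)**

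With the same true risk *p* in each arm and *n* participants per arm:

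- expected recorded events = *n* × *p* × detection probability
- apparent risk ratio = detection in a screened arm ÷ detection in standard of care

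Inputs: *n* = 150 (Abstract, approximate enrolment per cluster). Assumed: *p* = 5%; detection 90% with active screening; detection 90%, 60% or 30% without it.

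- True events per arm: 150 × 0.05 = 7.5
- Recorded in a screened arm: 7.5 × 0.90 = 6.75

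| Detection in standard of care | Recorded there | Apparent risk ratio |
|---|---|---|
| 90% | 7.5 × 0.90 = 6.75 | 0.90 / 0.90 = 1.0 |
| 60% | 7.5 × 0.60 = 4.5 | 0.90 / 0.60 = 1.5 |
| 30% | 7.5 × 0.30 = 2.25 | 0.90 / 0.30 = 3.0 |

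The ratio does not depend on *p*. At *p* = 2% or 10% the counts change (2.7 or 13.5 in a screened arm) but the ratios stay at 1.0, 1.5 and 3.0. The bias disappears only if detection without a screen matches detection with one.

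**The case against.** **No such comparison is planned.** This stands. Adverse events are not an outcome, and the Data Analysis Plan names no test of them. The Discussion ties scale-up to effectiveness and not to relative harm. The point therefore concerns what the adverse-event data could support, not an analysis in the plan.

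**Arm 3 is not left with the hotline alone.** This also stands. A reader might infer from the hotline sentence that calling in is the only route for standard of care. The Ethics section does not support that: it puts navigator reporting first, without limiting it by arm, and adds the hotline as a further route. Navigators also send retention reminders that are not limited by arm (Participant Recruitment and Retention). What arm 3 lacks in the text is a stated active screen. Large ratios built on a hotline-only premise, such as 80% capture against 10–30% (0.80/0.30 = 2.7 to 0.80/0.10 = 8), lose their basis.

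**Not every harm comparison is affected.** A reader might infer that any between-arm statement on harm is biased. Depression (PHQ-9) and perceived HIV-related stigma are secondary outcomes collected by survey at common time points, with no limit by arm, so they are not exposed to this problem. They are scale scores, however, and do not replace reports of testing-related events.

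**Arm 3 harms are not shown to go unmanaged.** The Ethics section relies on counselling at the testing clinics and gives all participants a list of community resources. The point concerns recording, not care.

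**The article is condensed.** The adverse-event forms it cites are not shown, and the full protocol may screen arm 3. That cannot be excluded. But the article is not silent on screening: it writes it into one arm's intervention and extends it to a second. Followed as written, the screen belongs to the kit visit.

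**Conclusion.** The concern holds as a limited point about safety reporting. The protocol states active adverse-event screening for arms 1 and 2 and states none for standard of care, while naming harms that can occur in all three. Adverse-event counts by arm would be open to unequal ascertainment. The likely direction is over-recording in the self-testing arms relative to standard of care, and arm 2's extra contact means that arms 1 and 2 are not fully alike either.

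The size cannot be taken from the document. The ratios of 1.0 to 3.0 rest wholly on assumed detection rates, and the range includes no distortion. The number of follow-up visits with a screen is not given, so contacts cannot be counted reliably.

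The primary and secondary efficacy outcomes are untouched. The conclusion assumes that the article describes the adverse-event procedure as carried out; a fuller protocol that screens arm 3 in the same way would remove the point.

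**What to change.** 1. Add a short set of identical, arm-neutral adverse-event items to the tablet survey for all three arms at the remaining waves: Time 3, and Time 2 for those not yet surveyed. The wording should cover any HIV testing or study contact and not self-testing alone.
2. Base any between-arm statement on harms only on these answers.
3. Keep the kit-specific screen in arms 1 and 2. List kit-specific events, replies of not fine, hotline calls and navigator reports separately and descriptively, without comparing them between arms.

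The article's Results section makes this feasible. By December 10, 2020, 295 of 452 participants had been followed up at wave 2, which left at most 452 − 295 = 157 to be asked at that wave, and wave 3 was due in February to March 2021.

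The cost is a few items in the existing survey form and a sentence in the reporting plan. The downsides are a slightly longer survey, and that participants who have already completed Time 2 can be asked only at Time 3, with a longer recall period.
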